## Abstract

**Background:**

Adolescents and young adults (AYAs) with cancer experience deficits in social connection that persist into survivorship; currently, few interventions target this unmet need. The current article describes the protocol for a pilot, parallel-group randomized controlled trial of a psychosocial intervention [Promoting Resilience in Stress Management (PRISM)] that includes a new skill-based module targeting AYA social needs (SN). The aims are to (1) establish the feasibility and acceptability of the PRISM-SN–adapted program; and (2) demonstrate proof-of-concept via clinically meaningful improvements in patient-reported outcomes (PROs).

**Methods:**

We anticipate 70 AYAs will enroll and complete data collection at two sites: Seattle Children’s Hospital and UPMC Children’s Hospital of Pittsburgh. Eligible AYAs are ages 12–25 years old; diagnosed with a new malignancy < 6 months; treatment plan includes chemotherapy and/or radiation; and are English-speaking. Enrolled AYAs are randomized 1:1 to receive PRISM-SN or usual care and complete surveys at baseline and 12-week follow-up. PRISM-SN includes 5 sessions (4 standard PRISM modules + new SN module) teaching behavioral skills associated with psychosocial wellbeing. Sessions are delivered 1:1 by a trained coach, in person or virtually, 1–2 weeks apart. Feasibility will be defined based on uptake, retention, and patient-reported intervention acceptability. Proof-of-concept will be defined based on clinically meaningful change and detectable differences in PROs at 12 weeks, including social relationship coping efficacy (primary PRO of interest), social support, quality of life, resilience, anxiety, depression, and hope. Descriptive statistics and covariate-adjusted regression models will be used to assess feasibility outcomes and examine trends and between-group differences in PROs across study arms.

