## Objectives and study design

This article describes the protocol of a pilot randomized-controlled trial (RCT) of the Promoting Resilience in Stress Management–Social Needs (PRISM-SN) adapted intervention among AYAs newly diagnosed with cancer**.** Our objectives are to assess the following: (1) feasibility, quantified via uptake, retention, and intervention acceptability; and (2) proof-of-concept, measured via minimal important difference on patient-reported outcomes (PROs) including SRCE (primary PRO of interest), social support, quality of life, hope, resilience, anxiety, and depression. For this pilot, parallel-group randomized trial, participants are randomized 1:1 to psychosocial usual care (UC, “control”) or PRISM-SN + UC (“intervention”) and complete PRO surveys at baseline and 12-week follow-up. We selected a pilot trial design with UC as our comparator to establish feasibility of delivering the PRISM-SN program in the context of a randomized trial and determine whether there is a signal of change in psychosocial outcomes in response to PRISM-SN compared to current standards of care. This protocol is reported following SPIRIT guidelines [55] adapted based on the CONSORT extension to pilot and feasibility trials [56] (Additional file 1).

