#### Patient-reported psychosocial outcomes

Our second aim is to explore trends and detectable between-group differences in psychosocial PROs at 12 weeks. Our primary PRO of interest is *Social Relationship Coping Efficacy (SRCE),* measured using the validated Cancer Behavior Inventory–Social Relationship Coping Efficacy subscale [54]. Ten items, on 1–9 Likert scale, assess confidence to engage in behaviors that maintain or enhance relationships in the context of illness. We also assess five secondary PROs. *Perceived Social Support* is measured using the Multidimensional Scale of Perceived Social Support [59]. This 12-item tool measures support from family, friends, and a significant other. *Quality of Life* is measured via the Patient-Reported Outcomes Measurement Information System (PROMIS) Pediatric Profile-25 (v2.0) [60]. This profile includes 25 items assessing health status across 7 domains: physical function mobility, anxiety, depressive symptoms, fatigue, peer relationships, pain interference, and pain intensity [61–64]; we also included an additional 4-items assessing family relationships (PROMIS Pediatric Family Relationships short-form v1.0) [65]. *Anxiety and depression* are measured using the Hospital Anxiety and Depression Scale [66]. *Self-perceived resilience* is measured using the 10-item Connor-Davidson Resilience Scale [67]. *Hope,* or the overall perception that one’s goals can be met, is measured using the 8-item Snyder Hope Scale [68].

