### Data analysis and sample size

Conservatively assuming 30% attrition due to illness, death, or dropout, we anticipate recruiting 100 AYAs over 2 years, with an evaluable sample of 70 (*N* = 35 per arm). This sample size will provide a margin of error ± 11% at 95% confidence for an estimated rate of 70%; for a rate of 80%, the margin of error is ± 9% at 95% confidence. This pilot trial is not powered to detect efficacy; data will be used to demonstrate intervention feasibility and proof-of-concept and inform the design of future larger randomized trials including benchmarks for accrual, retention, and intervention adherence.

Primary statistical analyses will be conducted on an intention-to-treat basis to avoid confounding by non-random participant attrition. To determine feasibility and acceptability (Study Objective 1), benchmark proportions and descriptive statistics will be used to examine uptake and retention rates and AIM scores. To determine proof-of-concept (Study Objective 2), demographics, clinical characteristics, and PRO items will be summarized at each time point using descriptive statistics: frequencies and proportions for categorical variables, means and standard deviations for continuous variables, or the median and interquartile range if the distribution is markedly skewed. Categorical outcomes will be compared between arms using the chi-squared test, and continuous outcomes will be compared using two-sample *t*-tests. In addition, covariate-adjusted linear regression models will be used to compare PROs between study arms, in which study arm is the predictor of interest and the stratification factors, site and age, are the covariates. For PROs without an established minimal clinically important difference (MCID), we will define minimal important differences as ½ standard deviation based on comparison samples [69].

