## Discussion

This paper describes the protocol for a pilot randomized trial to demonstrate feasibility and proof-of-concept for the Promoting Resilience in Stress Management–Social Needs (PRISM-SN) intervention. PRISM-SN is an adaptation of an established psychosocial program [28, 43] including a new component designed to enhance social connection for AYAs newly diagnosed with cancer [51]. Anticipated outcomes from this study include feasibility, measured by uptake, retention, and intervention acceptability, and proof-of-concept, determined based on improvements in patient-reported social outcomes at 12-week follow-up.

This study has important strengths related to the intervention and study design. Leveraging an already established and successful program [43, 45, 46, 70], PRISM-SN applies a novel, developmentally informed, skills-based approach to target social connection, a previously unmet need for AYAs with cancer. In addition, the two-site pilot randomized trial design has the potential to provide stronger evidence of feasibility compared to smaller single-arm studies. This study will demonstrate the feasibility of delivering the PRISM-SN program; of recruiting and retaining AYAs in both the UC and intervention trial arms; and of implementing this protocol at multiple national sites. In addition, feasibility outcomes from this study will inform benchmarks for uptake, retention, intervention adherence, and data completion for a subsequent multi-site efficacy trial.

Limitations of this protocol should also be noted. First, generalizability may be limited by study sites and the patient populations they serve. Both sites are academic, pediatric-based AYA oncology centers who serve patient populations with limited racial and ethnic diversity. Subsequent trials of this program will need to recruit larger, more diverse samples and determine whether this protocol is feasible at community-based or adult AYA cancer centers. Second, PRISM-SN is only available in English; translation to other languages is an important future direction. Third, this pilot trial will not be powered to test whether delivery adaptations to promote accessibility (i.e., in-person vs. virtual sessions, combining modules) affect response to the program.

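### Proof-of-concept (Objective 2) is defined in conflicting ways, and one definition asks for detectable differences in a trial stated not to be powered for efficacy

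*Protocol article*

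**What the plan says.** The article states the criterion for its second objective in several places:

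- **Abstract, Background:** the aim is proof-of-concept through clinically meaningful improvement in PROs.
- **Abstract, Methods:** "Proof-of-concept will be defined based on clinically meaningful change and detectable differences in PROs at 12 weeks". The list that follows has SRCE as primary PRO of interest, then social support, quality of life, resilience, anxiety, depression and hope.
- **Abstract, Discussion:** proof-of-concept comes from effects on social connection outcomes.
- **Objectives and study design:** "proof-of-concept, measured via minimal important difference on patient-reported outcomes (PROs) including SRCE (primary PRO of interest", followed by the other PROs. Detectability is not mentioned.
- **Patient-reported psychosocial outcomes:** "Our second aim is to explore trends and detectable between-group differences in psychosocial PROs at 12 weeks".
- **Discussion:** proof-of-concept is "determined based on improvements in patient-reported social outcomes at 12-week follow-up".

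Data analysis and sample size says "This pilot trial is not powered to detect efficacy; data will be used to demonstrate intervention feasibility and proof-of-concept". It plans descriptive summaries, chi-squared tests, two-sample t-tests and a linear regression of each PRO on arm, site and age. Where no established threshold exists, the minimal important difference is ½ SD from comparison samples. No alpha is given, *detectable* is not defined, and the number of PROs that must meet the criterion is not stated.

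**The concern.** Feasibility and acceptability each have one explicit cut-off (70% uptake, 70% retention, 80% of the intervention arm scoring at least 4). Proof-of-concept has several non-equivalent statements instead. They differ on which PROs count, on whether a size threshold applies, and on whether the difference must also be detectable.

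The verdict on Objective 2 is meant to inform larger trials. With several definitions in print, the one that fits can be chosen after the results are known. Keeping *detectable* as a condition also invites a reader to take a non-significant SRCE result as failure, although the article disclaims power for that comparison.

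**Working it through.** **1. The plan's own figures.** Margin of error with n = 70: 1.96 × √(0.7 × 0.3 / 70) = 10.7% and 1.96 × √(0.8 × 0.2 / 70) = 9.4%, matching the stated ±11% and ±9%. Recruitment: 70 / 0.70 = 100, as stated. These concern feasibility rates; no power is stated for any PRO.

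**2. The definitions side by side.**

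| Hypothetical 12-week result | Abstract, Methods | Objectives | Discussion |
|---|---|---|---|
| SRCE better by 0.3 SD, nothing else | Not met (below ½ SD) | Not met | Could be met (no threshold given) |
| Hope better by 0.6 SD and significant, social PROs unchanged | Could be met | Could be met | Not met |
| SRCE difference reaches its threshold but is not significant | Not met if *detectable* means significant | Met | Met |

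The third row needs a qualification. With 35 per arm the smallest significant difference is t(0.975, 68) × √(2/35) = 1.9955 × 0.2390 = 0.477 SD, so a ½ SD difference would normally be significant too. The row arises if the trial SD exceeds the comparison-sample SD by more than 0.5/0.477 = 1.048 (about 5%), if 31 or fewer per arm are evaluable (2.000 × √(2/31) = 0.508), or if an established threshold is below 0.477 SD. The first two rows need no such condition.

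**3. Power if *detectable* means significance.** Inputs: 35 per arm and ½ SD (Data analysis and sample size); two-sided 5% is assumed. Noncentrality = 0.5 × √(35/2) = 2.092.

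- Normal approximation: Φ(2.092 − 1.960) = 55.2%.
- Noncentral t, 68 df: 54.1%, so a true ½ SD effect is missed 46% of the time.
- One-sided 5%: power 66.5%, miss 34%.
- Also requiring an observed difference of at least ½ SD: miss 50%, because the estimate is symmetric about the true value.
- Two-sided 5% with baseline adjustment, which the planned model does not list: miss 34% if the baseline-to-12-week correlation is 0.5, and 18% if it is 0.7.

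**4. Chance success if any one PRO sufficed.** Score count from the outcomes section: SRCE 1, social support 1, PROMIS domains 7, family relationships 1, anxiety and depression 2, resilience 1, hope 1; total 14. With no effect, the chance that one score shows a favourable difference of at least ½ SD is 1 − Φ(0.5/0.2390) = 1.82%.

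- 14 independent scores: 1 − (1 − 0.0182)^14 = 23%.
- Equal correlation 0.3 / 0.5 / 0.7 (simulated, 200,000 draws): 18% / 14% / 10%.
- Counting only the article's six PROs (one primary, five secondary) as independent: 1 − (1 − 0.0182)^6 = 10%.

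**The case against.** The strongest reply is that this is a pilot that openly disclaims power, calls its second aim exploratory and names SRCE as primary. The aims in the Abstract and the Objectives section broadly agree with each other, and the Discussion sentence is only a summary. Alpha, multiplicity handling and operational thresholds commonly sit in a full protocol or analysis plan, which is not shown.

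Much of that stands. A reader might infer that proof-of-concept can be claimed on any one of about 14 scores. No section says so, the Abstract joins detectability to clinically meaningful change, and SRCE is singled out. A reader might also take *detectable* to mean p < 0.05. The planned tests make that natural, but the article never defines the word, so the power figure is conditional. Nor can it be said that the minimal important difference goes unused: the Objectives section makes it the measure of proof-of-concept.

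The reply does not remove the conflict itself. The statements are all in the published text, and a more detailed plan can settle them only by overriding some. Naming SRCE primary does not make it decisive, because the Abstract and the Objectives both place the other PROs under the same criterion.

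**Conclusion.** The concern holds as a conflict between stated criteria. The sections differ on which PROs count, on the size required and on whether detectability is needed, so one data set can give opposite verdicts on Objective 2.

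The *detectable* condition does not fit a trial declared not powered for efficacy. On an assumed two-sided 5% test with 35 per arm, power at ½ SD is about 54% (miss 46%; 34% at one-sided 5%). The 10–23% chance of spurious success applies only if any one of 14 scores were enough, which the text leaves open but does not state; the range reflects correlations from 0.7 down to 0.

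This should be corrected, because it determines what the trial will be said to have shown.

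**What to change.** State proof-of-concept once, and align the Abstract (Background, Methods and Discussion), Objectives and study design, Patient-reported psychosocial outcomes, and the main Discussion with it:

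- **Measure:** the between-arm difference in SRCE at 12 weeks, from the planned regression with the baseline SRCE score added to site and age.
- **Reading:** the estimate with its 95% CI, against an SRCE minimal important difference fixed before the statisticians are unblinded.
- **Wording:** drop *detectable* as a criterion.
- **Other PROs:** supportive estimates with CIs.

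**Cost.** No added participants or data, since SRCE is already collected before randomization. It is more than an edit of wording: one covariate is added and a numerical SRCE threshold must be set. No proof-of-concept claim could then rest on a secondary PRO.

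**What it does not do.** An estimate-reaches-threshold rule still misses a true effect exactly at the threshold 50% of the time, so the CI must accompany the verdict. Without baseline adjustment its half-width is about ±0.48 SD; at a baseline correlation of 0.5 it would be about 0.48 × √(1 − 0.25) = ±0.41 SD. The gain is one fixed rule, with no route to success through multiple outcomes.

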**Discussion:**

This pilot trial will determine feasibility of PRISM-SN in the context of a multi-site trial; provide proof-of-concept via effects of PRISM-SN on social connection outcomes; and represent an important step toward addressing an unmet need in AYA cancer care. Future directions include testing efficacy and effectiveness via larger multicenter trials.

**Trial registration:**

ClinicalTrials.gov Identifier NCT06242964

**Supplementary Information:**

The online version contains supplementary material available at 10.1186/s40814-026-01775-0.

## Background

Adolescents and young adults (AYAs) with cancer experience deficits in social connection which persist into survivorship [1–3]. Social connection is an umbrella term that encompasses the structure, function, and quality of one’s social relationships [4]. Compared to healthy peers, AYAs with cancer report lower social quality of life and social functioning at diagnosis and 2 years later [3, 5]. Many experience social isolation and insufficient social support [6–8], describe feeling distant from peers [9, 10], report challenges navigating illness-related stressors in close relationships [10, 11] and rank supportive care resources to enhance social connection as a top priority [1, 12, 13]. Given well-established links between social connection and both physical and mental health [14–17], addressing this need may be an important avenue for improving long-term outcomes.

Existing psychosocial and behavioral interventions have been limited in their ability to improve social connection among AYAs [18]. Intervention approaches have primarily included support groups [19], group-based social activities [20, 21], or group-based delivery of psychological treatments or interventions [22, 23]. Most programs target social support via connecting AYAs with one another; fewer consider support from other interpersonal relationships or target other aspects of social connection, which may limit overall success. For example, though support from other AYAs is valuable [11, 12, 24], AYAs also derive support from other consequential relationships including family members and healthy peers [10, 11, 25]. Cancer-related challenges in these relationships are common [1, 11, 25], may exceed AYAs’ still-developing socioemotional skills [26, 27], and thus contribute to a range of social connection deficits such as social isolation, poor social functioning, and inadequate support. Novel, more comprehensive approaches for addressing social connection in the AYA population are needed.

Individually delivered, skill-based interventions such as the Promoting Resilience in Stress Management (PRISM) program [28] have successfully improved psychosocial outcomes among AYAs with serious illness. Informed by stress and coping and resilience theories [29–32], Cognitive-Behavioral Therapy, and positive psychology interventions [33–39], PRISM is a lay coach-led intervention delivered in a brief, 1:1 format, teaching actionable behavioral skills associated with wellbeing [28, 40]. PRISM has been shown to be feasible, acceptable [28, 41, 42] and efficacious in improving resilience, hope, and quality-of-life and reducing distress among AYAs with cancer or other serious illness [43–46]. As designed, PRISM does not directly target social connection; however, its multi-component, skill-based framework and established success allow for adaptation and expansion. Given robust associations between social connection and other aspects of wellbeing [6, 14, 47, 48], expanding the PRISM program to include a component addressing AYAs’ social needs has the potential to increase the comprehensiveness and efficacy of the program while addressing a critical need in AYA cancer care.

We followed the ORBIT model for behavioral treatment development [49] and patient-centered intervention design principles [50] to create a novel PRISM module to enhance social connection among AYAs with cancer [51]. ORBIT is a flexible, progressive model for translating basic social sciences research to health-related behavioral treatments, with phases ranging from initial design to effectiveness testing [49]. Fulfilling the goals of ORBIT Phase I (Design: Define & Refine), we applied theories of self-efficacy and behavior change [52, 53], findings from preliminary and extant research on AYA social connection [1, 9–11, 25], and AYA stakeholder input to develop a skill-based PRISM module to enhance AYAs’ social relationship coping efficacy (SRCE) [54]. SRCE is defined as the confidence in one’s ability to engage in behaviors that foster, maintain, or enhance close social relationships in the context of cancer. SRCE represents a proximal outcome that is associated with a variety of downstream indicators of social connection (i.e., social support, social quality of life) and psychological wellbeing for individuals with cancer [54] and can be targeted through an individual behavioral intervention such as PRISM. Module content was acceptable among AYA stakeholders when delivered individually and as part of the PRISM program [51].

## Objectives and study design

This article describes the protocol of a pilot randomized-controlled trial (RCT) of the Promoting Resilience in Stress Management–Social Needs (PRISM-SN) adapted intervention among AYAs newly diagnosed with cancer**.** Our objectives are to assess the following: (1) feasibility, quantified via uptake, retention, and intervention acceptability; and (2) proof-of-concept, measured via minimal important difference on patient-reported outcomes (PROs) including SRCE (primary PRO of interest), social support, quality of life, hope, resilience, anxiety, and depression. For this pilot, parallel-group randomized trial, participants are randomized 1:1 to psychosocial usual care (UC, “control”) or PRISM-SN + UC (“intervention”) and complete PRO surveys at baseline and 12-week follow-up. We selected a pilot trial design with UC as our comparator to establish feasibility of delivering the PRISM-SN program in the context of a randomized trial and determine whether there is a signal of change in psychosocial outcomes in response to PRISM-SN compared to current standards of care. This protocol is reported following SPIRIT guidelines [55] adapted based on the CONSORT extension to pilot and feasibility trials [56] (Additional file 1).

## Method

### Participants and procedures

Participants are recruited from two academic pediatric oncology centers in the United States: Seattle Children’s Hospital (SCH) and University of Pittsburgh Medical Center (UPMC) Children’s Hospital of Pittsburgh. To be eligible, AYAs must be 12–25 years old; diagnosed with a new malignancy treated with chemotherapy and/or radiation in the past 6 months; able to speak and read English; and cognitively able to complete the intervention and surveys. Concomitant psychological or psychiatric care and/or other psychosocial interventions are permitted during the trial, though AYAs may not have had previous exposure to or be co-enrolled in other studies of the PRISM program. Potentially eligible AYAs are identified by screening outpatient clinic and inpatient rosters, and eligibility is confirmed via electronic health record review. Eligible AYAs (and a parent or legal guardian, if < 18 years old) are then approached by study staff in person during a clinic visit or inpatient stay to introduce the study and obtain informed consent (AYAs ≥ 18 years old, parents of those younger) and written assent (AYAs 12–17 years old). Strategies to promote enrollment include utilizing in-person approaches; communicating with providers regarding ideal times for approach; and providing the option to complete consent conferences virtually/using electronic signatures after the initial in-person approach.

Participant timeline is described in Fig. 1. Enrolled participants on both arms complete a survey containing a demographic questionnaire and a PRO battery at baseline (pre-randomization) and at 12-week follow-up. Surveys are administered via Research Electronic Data Capture (REDCap) [57] or paper and pencil upon request and must be completed within 4 weeks. Incentives of $25 and $50 are provided for baseline and follow-up surveys, respectively, and participants on both arms receive a small non-monetary incentive (e.g., tote bag or water bottle with the study logo) during their participation. To promote retention and follow-up, study staff contact participants via email, phone, or in-person check-ins to notify them of an upcoming survey due date and confirm how they would like to complete the survey (e.g., email link, study tablet provided during clinic visit, paper and pencil). Thereafter, staff provide weekly reminders for outstanding surveys. Clinical information is abstracted from electronic health records each month throughout the study period, including diagnosis, diagnosis date, treatment modalities and intensity, any pre-existing or current psychiatric diagnoses, and any formal psychological treatment received during study participation. Participants may be taken off study if they request to withdraw, do not complete study activities within the specified timeframe, are unable to be reached by study staff for > 4 weeks, or are deceased before completing study activities. For participants who request to withdraw from the study, study staff ask for and document reasons for withdrawal.

